### Inclusion criteria

To be eligible, participants must meet the following conditions: (1) patients must be 35–80 years old, with a recent (30–40 days) ischaemic stroke; (2) patients should have a National Institutes of Health Stroke Scale (NIHSS) score between 4 and 24; (3) the stroke should be the first incidence or patients can have a history of stroke, but must be without disability (modified Rankin Scale, mRS score ≤1).

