### Outcome assessment

The assessment data will be collected at baseline, 4 and 8 weeks postrandomisation, and then 12 weeks after completing the treatment.

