### Primary outcome measurement

The primary outcome measure is the Modified Barthel Index (MBI), which was developed in 1955 as a simple index of independence useful in scoring disability.^8^ The MBI scale is a reliable measure of functional independence. It is sensitive and valid to evaluate dependence in the activities of daily living (ADL). It includes 10 variables (defecating, urinating, feeding, bathing, grooming, dressing, toileting, transfer, walking and using stairs) describing ADL and mobility. A higher number is associated with a greater likelihood of being able to live at home with a degree of independence. This index is used as a standardised assessment on rehabilitation wards and also as standardised follow-up assessment to determine whether gains achieved by patients with stroke while hospitalised are maintained after discharge.^9–11^

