### Sample size calculation

The primary efficacy parameter is the change in MBI scores from baseline to the end of treatment after 8 weeks. Sample size calculations are based on our preliminary test and previous study.^21^
^22^ The expected difference between CR group and IMR group is a 10 value, that is to say the score of MBI of the IMR group was a 10 value higher than that of the CR group, and the SD is about 31. A two sided 5% significance level and 80% power were considered, and the following equation was used:
[figure not shown]

Approximately 150 participants in each group were calculated to be required. Estimating a 20% dropout rate, each group will require 180 initial participants.

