### Statistical analysis

Efficacy and safety analyses will be conducted according to the intention-to-treat (ITT) principle by a statistician blinded to group allocation. Missing values will be imputed by the last-observation-carried-forward method. All statistical analyses will be performed using Statistical Product and Service Solutions (SPSS) statistical package program (V.17.0, SPSS Inc, Chicago, Illinois, USA). The primary outcomes (MBI) and FMA will undergo ITT analysis including all the patients who are randomised. The analysis of cognitive impairment and emotional disorder will be made among the defined population of corresponding dysfunction. Continuous variables will be expressed as means with SDs. For normally distributed variables, two independent samples will be compared by independent sample t test. On the other hand, for abnormally distributed variables, non-parametric tests will be used and the data will be expressed as medians with ranges. A p value of less than 0.05 is considered as statistical significance. Safety analysis is based on the frequency of AEs relating to the treatment.

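### The MBI analysis keeps every randomised patient and carries forward every missing value, so a patient who dies is scored with the last living MBI, and no all-cause comparison of deaths is planned

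*Protocol article*

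**What the plan says.** The Statistical analysis section fixes who is analysed and how gaps are filled:

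- Population: "The primary outcomes (MBI) and FMA will undergo ITT analysis including all the patients who are randomised".
- Missing data: "Missing values will be imputed by the last-observation-carried-forward method". No reason for missingness is exempted.
- Safety: "Safety analysis is based on the frequency of AEs relating to the treatment".

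The Sample size calculation section defines the endpoint: "The primary efficacy parameter is the change in MBI scores from baseline to the end of treatment after 8 weeks". The Outcome assessment section gives the visits: "The assessment data will be collected at baseline, 4 and 8 weeks postrandomisation, and then 12 weeks after completing the treatment". Week 4 is therefore the only assessment between baseline and the primary time point, and the last visit falls at 8 + 12 = 20 weeks. The article does not mention death in connection with the MBI: it gives no worst score, no composite and no while-alive definition.

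**The concern.** After dropout a true MBI exists but is not seen. After death there is none. The two situations need different rules, and the plan has one rule for both. The MBI measures independence in daily living, and the Primary outcome measurement section says of it that "A higher number is associated with a greater likelihood of being able to live at home with a degree of independence". Recording a death as unchanged or improved function does not fit that meaning.

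Replacing LOCF with a mixed model or multiple imputation would not cure this, because those methods would also score the dead as if alive.

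Some deaths are plausible. Patients are aged up to 80, are 30-40 days past an ischaemic stroke, and on severity "patients should have a National Institutes of Health Stroke Scale (NIHSS) score between 4 and 24". If more patients die in one arm, the planned MBI comparison gives that little weight. A death judged unrelated to treatment is also outside the stated safety count, so neither planned analysis would compare total deaths between arms.

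**Working it through.** **Inputs from the protocol article.** Planned difference 10 points ("The expected difference between CR group and IMR group is a 10 value"), SD about 31, two-sided 5% level, 80% power and 180 per arm after allowance for dropout (Sample size calculation); analysis population and LOCF (Statistical analysis); visit times (Outcome assessment).

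**Assumptions, because the article gives no figure.** MBI range 0-100 with 0 worst; last living score L of 40-60 (30-60 for the wider range); numbers of deaths. The article states no mortality rate and no baseline MBI.

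**The plan's own figure.** n per arm = 2 × (1.960 + 0.842)² × 31² / 10² = 150.9, so 151, against the stated figure of about 150. It reproduces, and the point here does not change it.

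**What LOCF does, by time of death.**

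- Before week 4: the baseline score B is carried, so the week-8 change is B − B = 0.
- Between weeks 4 and 8: the week-4 score is carried, so the week-8 change equals the week-4 change. That is a gain if the patient had improved and a loss if the patient had worsened.
- After week 8: the primary endpoint is untouched, but the week-8 score stands in for the week-20 value.

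**Gap against a worst score.** Under LOCF a dead patient's change is L − B. With death scored 0 it is 0 − B. The gap is L, so each death shifts its arm's mean by L/180:

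- L = 40: 40/180 = 0.22 points.
- L = 60: 60/180 = 0.33 points.

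**Imbalance between arms, with equal L.**

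- Three more deaths in one arm: 3 × 40/180 = 0.67 to 3 × 60/180 = 1.00 points.
- Five more deaths: 5 × 40/180 = 1.11 to 5 × 60/180 = 1.67 points, or 11-17% of the planned 10.

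**Scale.** The standard error of the difference is 31 × √(2/180) = 3.27. Three deaths move the contrast by 0.67/3.27 = 0.20 to 1.00/3.27 = 0.31 standard errors. Five move it by 1.11/3.27 = 0.34 to 1.67/3.27 = 0.51.

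**As proportions.** The contrast (IMR minus CR) shifts by dI × LI − dC × LC, where d is the proportion dying in each arm. With L of 30-60 in both arms:

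- Deaths of 3% in IMR and 1% in CR: 0.02 × 30 = 0.6 to 0.02 × 60 = 1.2 points.
- Deaths of 5% and 1%: 0.04 × 30 = 1.2 to 0.04 × 60 = 2.4 points.
- Equal d and equal L: no shift. If more die in the CR group, the sign reverses.

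**Does a death make an arm look better?** Assume survivors gain 30 (IMR) and 20 (CR), B = 30, no gain by week 4, and deaths of 3% in IMR and 1% in CR.

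- Under LOCF: 0.97 × 30 − 0.99 × 20 = 29.1 − 19.8 = 9.3.
- With death scored 0: (29.1 − 0.03 × 30) − (19.8 − 0.01 × 30) = 28.2 − 19.5 = 8.7.

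LOCF still takes the contrast below the survivors' 10. It takes it down by less than the worst-score rule does, and the gap of 0.6 equals 0.02 × 30.

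**The case against.** **This could be left to the analysis plan.** The article is condensed and never names death, and a scoring rule for deaths is often set in the SAP, which is not shown. That has some force. But the article does state a rule, and an SAP that treated deaths differently would have to override it. The point rests on what that rule does, not on silence.

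**A reader might infer that deaths make an arm look better.** The documents do not support this. The endpoint is change from baseline in patients expected to gain. A carried zero or week-4 change will usually lie below the survivors' mean week-8 change, so a death usually lowers its arm's mean. It would raise the mean only if the carried change exceeded the average change of the others. The under-penalty exists relative to a worst-outcome score.

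**A reader might also infer that an excess of deaths would go unnoticed.** The documents do not support this either. The section on adverse events has all events recorded and serious ones reported at once to the principal investigator and ethics committee. Quality control describes monthly monitoring that covers adverse events, and the abstract lists adverse-event incidence as a secondary outcome. What remains is narrower: the stated safety analysis is limited by relatedness.

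**The effect may be small.** Serious heart, liver and kidney disease are excluded, patients enter 30-40 days after the stroke, treatment is given as inpatients, and the primary time point is week 8. Deaths by then may be few, and fewer than the 20% planned for dropout. This stands, and it limits the size of the point.

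**Scoring death as 0 is a choice of estimand.** This also stands. It mixes function with survival, and the penalty depends on baseline: a patient at 90 loses 90 points, one at 10 loses 10. It should not be presented as the only acceptable primary rule.

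**Conclusion.** The point holds in a limited form. As written, the plan gives patients who die an MBI change that has no meaning: zero for a death before week 4, the week-4 change for a death between weeks 4 and 8. Measured against a worst-outcome score, an arm with more deaths is under-penalised by 0.22-0.33 points per death and by 1.1-1.7 points for an imbalance of five, which is at most about half a standard error. These sizes rest on an assumed 0-100 range, a last living score of 40-60 and 180 analysed per arm. With balanced deaths and similar last scores the contrast hardly moves. Such a shift could matter to a borderline result but would not on its own create or remove an effect of the planned size. Separately, the stated analyses contain no all-cause comparison of deaths by arm. The plan should be changed, mainly because the rule is wrong in kind and nearly free to correct before unblinding.

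**What to change.** Amend the Statistical analysis section as follows:

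- State that death is not a missing value and that no MBI is carried forward past it.
- From the time of death, score the patient at the worst MBI (0) or assign the worst rank. Do this in the primary analysis or, at the least, in a prespecified sensitivity analysis. Worst rank avoids a penalty that depends on baseline and suits the non-parametric tests that the section already allows.
- Present survivors-only results alongside.
- Report all-cause deaths by arm at weeks 8 and 20, whatever their judged relation to treatment.

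If the worst-score rule is kept to the sensitivity analysis, the primary analysis still needs a stated way of handling deaths other than LOCF.

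The cost is a few sentences, with no change to visits, sample size or care. Where the worst score is used, the variance rises slightly and the endpoint combines function with survival. The report should say so.

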### Baseline assessment

Demographic data includes gender, age, nationality, education level, occupation and marital status. Information on stroke risk factors regarding smoking, drinking, height, weight, blood pressure, family history of stroke, blood lipids and blood sugar is gathered through review of the medical records. Several classifications of disease data regarding: rehabilitation evaluation scales on neurological deficit, sensory motor, and cognitive and emotional disorders will be also analysed before randomisation.

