#### The mini-mental state examination and Montreal Cognitive Assessment (MoCA) for cognitive impairment

Cognitive function is assessed by the mini-mental state examination (MMSE) and MoCA scale. MMSE is a brief wide-range screening test with 30 aggregate scores, which is more suitable for uneducated or old populations. It assesses memory, orientation, calculation attention span, and ability to express and to read. In fact, MMSE is widely used because of its high specificity, but it cannot subtly detect patients with mild cognitive impairment (MCI), whose scores are in the normal range.^16^ In contrast, MoCA is more sensitive. It is also a test with 30 points, of which items include visual-spatial abilities, executive functions, attention span, concentration, memory, language and orientation. The MoCA detects patients with MCI with 90% sensitivity and 87% specificity.^17^

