#### The Self-Rating Depression Scale and Hamilton's Depression Scale for emotional disorder

Self-Rating Depression Scale (SDS) is a self-report instrument covering 20 items, either positive or negative, with a four-point scale ranging from 1 to 4. The standardised score is the total score times 1.25, which results in 25–100.^18^ Furthermore, in antidepressant clinical trials, the Hamilton Depression Rating Scale has been the ‘gold standard’ for use.^19^ The Hamilton's Depression Scale (HAMD) Scale we selected includes 24 items, consisting of sense of guilt, sleeping problems, suicide, lack of interest, anxiety, loss of weight, self-abasement, hopelessness, and so on; 14 items with a score of 0–4 and 10 items with a score of 0–2. The range of scores for the whole test is 0–76. Higher scores indicate a higher level of mental disorder.^20^

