## Conclusion

This trial has been designed to provide robust data on the efficacy of IM for patients with ischaemic stroke. It is also expected to clarify whether or not IM is effective for motor, cognitive or emotional disorder after stroke.

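### MMSE, MoCA, HAMD and SDS are compared only in patients with the matching dysfunction; an all-randomised comparison should stand beside that subset analysis

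*Protocol article*

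**What the plan says.** The Statistical analysis section opens with a general rule: "Efficacy and safety analyses will be conducted according to the intention-to-treat (ITT) principle". It then treats the outcomes in two ways. For the first group, "The primary outcomes (MBI) and FMA will undergo ITT analysis including all the patients who are randomised". For the second, "The analysis of cognitive impairment and emotional disorder will be made among the defined population of corresponding dysfunction".

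The secondary outcome sections identify the scales in the second group. "Cognitive function is assessed by the mini-mental state examination (MMSE) and MoCA scale", and SDS and HAMD are the scales for mood (section heading: "The Self-Rating Depression Scale and Hamilton's Depression Scale for emotional disorder"). That is four of the six secondary scales; the other two are NIHSS and FMA. The abstract lists all six as secondary outcomes and attaches no subset to any of them.

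The Baseline assessment section says that scales for "cognitive and emotional disorders will be also analysed before randomisation", so a classification made before randomisation is possible. The Conclusion expects the trial to "clarify whether or not IM is effective for motor, cognitive or emotional disorder after stroke".

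**The concern.** The eligibility criteria require neither cognitive nor mood impairment, so some randomised patients will fall outside these populations. Those allocated to the integrative arm still receive eight weeks of acupuncture and herbs. As the rule is written, no planned comparison on the four scales includes them.

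A patient who enters without depression or cognitive impairment and develops either during the 20 weeks would not be seen in a subset defined at baseline. The trial could then report benefit in affected patients while a preventive effect, or an opposite effect, in the others went unexamined on these scales. The closing claim about disorder after stroke could also be read as covering more patients than the analysis does.

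The safety analysis does not make up for this. Adverse events are asked of all participants at each visit, but the analysis counts only those related to treatment. Depression or cognitive decline attributed to the stroke would not be counted.

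**Working it through.** **1. The plan's own figure.** Inputs from Sample size calculation: difference 10 MBI points, SD 31, two-sided 5%, power 80%.

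n per group = 2 × (1.96 + 0.84)² × 31² / 10² ≈ 151. The article states about 150, so it reproduces; power at 150 is 79.8%. This figure concerns MBI only. The article gives no calculation for the four scales.

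**2. Detectable difference on the four scales.** The affected share is not given, so it is varied here as an assumption. With m patients per arm, the standardised difference detectable at 80% power is (1.96 + 0.84) × √(2/m). The power column uses the planned MBI effect, 10/31 = 0.32 SD, as a yardstick only. All figures are before dropout.

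| Affected share | m per arm | Outside the comparison (of 360) | Detectable difference (SD) | Power at 0.32 SD |
|---|---|---|---|---|
| 20% | 36 | 288 | 0.66 | 28% |
| 30% | 54 | 252 | 0.54 | 39% |
| 50% | 90 | 180 | 0.42 | 58% |
| 70% | 126 | 108 | 0.35 | 73% |
| all randomised | 180 | 0 | 0.30 | 86% |

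With 20% loss (144 per arm), the detectable difference is 0.60, 0.47 and 0.39 SD at 30%, 50% and 70%, against 0.33 SD with everyone.

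**3. What each analysis can see.** Illustrative assumptions: 180 per arm, baseline and follow-up SD 1, correlation 0.6, and affected patients being the worst-scoring 40% at baseline (72 per arm).

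- Subset, change score: the variance of baseline within the worst 40% of a normal distribution is 0.31. The variance of change is (1 − 0.6)² × 0.31 + (1 − 0.6²) = 0.69, so SD = 0.83 and SE = 0.83 × √(2/72) = 0.138.
- All randomised, baseline-adjusted: SD = √(1 − 0.6²) = 0.80, SE = 0.80 × √(2/180) = 0.084.
- All randomised, change score: SD = √(2 × (1 − 0.6)) = 0.894, SE = 0.894 × √(2/180) = 0.094.

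| Assumed effect | Subset, change score | All randomised, baseline-adjusted |
|---|---|---|
| 0.3 SD benefit in everyone | 58% | 95% |
| 0.3 SD harm in unaffected patients only | 5% | 56% |
| 0.5 SD benefit in affected patients only | 95% | 63% |

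The table shows simulated rejection rates (4000 trials per row). The formulas agree. In row 1, 0.3/0.138 = 2.17 gives 58% and 0.3/0.084 = 3.56 gives 94%. In row 2 the subset effect is zero, so it rejects at the 5% level, while the average effect over everyone is 0.6 × 0.3 = 0.18 SD, giving 57%. In row 3 the average is 0.4 × 0.5 = 0.20 SD, giving 66%; the simulated figure is slightly lower because the unequal effect adds variance.

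The first row changes both the population and the adjustment. The change score in all randomised patients gives 0.3/0.094 = 3.18, or 89%. So 58% to 89% comes from the population and 89% to 95% from the adjustment.

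**The case against.** A reader might infer that the restriction contradicts the plan's intention-to-treat rule. The documents do not support that. If dysfunction is classified before randomisation, which the Baseline assessment section makes possible, comparing everyone in the subset as allocated is a proper randomised comparison for a narrower question. Lack of stratification by dysfunction would not bias it. Only membership set from later data would break the randomised comparison, and the article does not say that this will happen. It states the exception openly in the same paragraph as the general rule. The cut-off may stand in the full protocol or analysis plan, which are not shown, so its absence here is not part of the point.

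The different treatment of FMA also has a rationale. Physical and occupational therapy and the base acupuncture points go to everyone in the relevant arm. Cognitive training, counselling and the added cognitive or emotional acupoints go only to affected patients. The Discussion speaks of recovery from impairment. Where the effect lies only in affected patients, the planned subset is the stronger analysis, 95% against 63% in the illustration. This all stands, and it is why the subset should be kept.

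Two other strong readings also fail. It cannot be said that decline in the other patients is never looked at, since adverse events are collected from all participants. Nor can it be said that most of the randomised information goes unused: at 70% affected, only 108 of 360 patients fall outside. The common-benefit scenario is a best case, because unaffected patients have little room to improve on scales with ceilings and floors.

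What remains is that patients outside the subset are randomised and exposed, and that no planned comparison on the four scales includes them.

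**Conclusion.** The point holds as a limit of coverage. The four scales are compared in a narrower population than MBI and FMA, and neither the scale analyses nor the treatment-related event counts would show new or worsening cognitive or mood problems in the other randomised patients. This assumes that membership is fixed before randomisation; patients who already have the dysfunction at baseline are compared, including for worsening.

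The loss of precision is modest if most patients are affected and substantial if few are. No single figure can be given, because the affected share is unknown. The outcomes are secondary and the primary MBI analysis is untouched, so severity is low to moderate.

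**What to change.** In the Statistical analysis section:

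1. Keep the dysfunction-population analysis for the recovery aim, and state that membership is fixed only by the pre-randomisation assessment.
2. Add a pre-specified comparison of MMSE, MoCA, HAMD and SDS in all randomised patients with post-baseline scores.
3. Adjust both analyses for the baseline score of the scale concerned.
4. In the Conclusion, limit each statement to the population its analysis covers.

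The cost is a few sentences and four more models. The added estimate is diluted if the effect exists only in affected patients, so it should stand beside the subset result and not replace it.

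The addition is possible only where the scales were given to unaffected patients after baseline. The article schedules four assessment visits but does not say whether these patients complete the four scales at each, and its recruitment period ended on 31 December 2014, so missed scores may not be recoverable. The plan's last-observation-carried-forward rule would not help, since repeating a baseline score only records no change. If the scores do not exist, the conclusion should be limited to patients with the dysfunction at baseline.

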**Methods and analysis:**

360 participants recruited from three large Chinese medical hospitals in Zhejiang Province will be randomly divided into the integrative medicine rehabilitation (IMR) group and the conventional rehabilitation (CR) group in a 1:1 ratio. Participants in the IMR group will receive acupuncture and Chinese herbs in addition to basic Western medicine and rehabilitation treatment. The CR group will not receive acupuncture and Chinese herbal medicine. The assessment data will be collected at baseline, 4 and 8 weeks postrandomisation, and then at 12 weeks’ follow-up. The primary outcome is measured by the Modified Barthel Index. The secondary outcomes are the National Institutes of Health Stroke Scale (NIHSS), Fugl-Meyer Assessment, the mini-mental state examination and Montreal Cognitive, Hamilton's Depression Scale and Self-Rating Depression Scale, and the incidence of adverse events.

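### The observed distribution decides whether the primary outcome is reported as a mean difference or as medians with a rank test, although the trial is sized on a mean difference

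*Protocol article*

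**What the plan says.** The Sample size calculation section of the protocol article defines the primary variable: "The primary efficacy parameter is the change in MBI scores from baseline to the end of treatment after 8 weeks". It sizes the trial on a difference between groups: "The expected difference between CR group and IMR group is a 10 value", and "the SD is about 31". The error rates follow: "A two sided 5% significance level and 80% power were considered". The result is "Approximately 150 participants in each group were calculated to be required", raised for losses: "Estimating a 20% dropout rate, each group will require 180 initial participants".

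The Statistical analysis section then gives a single rule for continuous variables. Normally distributed variables are compared by an independent-sample t test. Otherwise, "for abnormally distributed variables, non-parametric tests will be used and the data will be expressed as medians with ranges". It names no separate test for the MBI. The same section calls for an intention-to-treat analysis of all randomised patients, fills missing values by carrying the last observation forward, and assigns the analysis to a statistician who does not know the allocation.

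**The concern.** The primary comparison has two branches, and the collected data choose between them. The t-test branch compares mean change, which is what the 10-point assumption describes. The other branch reports two medians with their ranges and a p value from an unnamed rank test. Two medians do not estimate a difference in means, and a range is not a measure of precision. A trial designed to detect 10 points might therefore publish a primary result that cannot be set against those 10 points. Different scales or visits within the trial could also be summarised in different ways.

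The variable, the time point and the analysis population stay the same on both branches. What is left open is the population summary and the test that goes with it.

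**Working it through.** **1. Reproduce the planned size.** Inputs from the Sample size calculation section: difference 10, SD 31, two-sided 5%, 80% power. The abstract gives the allocation: "conventional rehabilitation (CR) group in a 1:1 ratio".

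n per group = 2 × (1.960 + 0.842)² × 31² / 10² = 2 × 7.849 × 961 / 100 = 150.9, so 151. The plan's figure of about 150 is confirmed.

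Power at 150 per group: 10 / (31 × √(2/150)) = 10 / 3.580 = 2.794; 2.794 − 1.960 = 0.834; Φ(0.834) = 79.8%.

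This is a calculation for a comparison of means. If a rank test were fixed instead and the data were normal, the asymptotic relative efficiency of 3/π would give 151 / 0.955 = 158.1, so 159 per group.

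**2. How often the rule would switch with complete data.** The article gives no normality criterion. Assumption: Shapiro-Wilk at 5% in each arm, with a switch to Mann-Whitney if either arm rejects. With exactly normal data, the chance that at least one of two arms rejects is 1 − 0.95² = 9.75%.

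Simulation at 150 per arm, with MBI assumed to lie between 0 and 100, baseline SD 25, week-8 SD 31, correlation 0.6–0.7 and week-8 mean 60–75, gives a switch for the change in about 9–12% of trials. That is close to the false-positive rate of the normality test itself. The rule switches and also alters statistical significance in about 1% of trials or fewer.

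**3. Effect on error rates.** 4,000 simulated trials at 150 per arm, rule against t test alone:

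| Assumed distribution of change | Rank test chosen | Type I error, rule / t test | Power, rule / t test |
|---|---|---|---|
| Normal, SD 31 | about 10% | 5.35% / 5.2% | 79% / 79% |
| Bounded 0–100 scale | about 16% | 4.8% / 4.7% | 93% / 93% |
| Skewed (gamma) | 100% | 4.6% / 4.8% | 92% / 80% |

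Type I error is barely affected in any row. The t test also holds its level in the skewed case, so the switch is not needed to protect it.

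**4. Interaction with the missing-data rule.** The Outcome assessment section places visits at baseline, 4 weeks and 8 weeks. A patient lost before week 4 has only a baseline value. Carrying it forward makes the 8-week change exactly zero, and a group of such patients forms a spike that a normality test detects. The plan expects 20% dropout. How much of that falls before week 4 is not stated, so the share with baseline carried forward could lie anywhere from 0 to 20%. Of 180 per arm, 10% is 18 patients and 20% is 36.

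Simulation at 180 per arm, same assumptions as step 2:

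- 10% with baseline carried forward: the rule switches in about 80–95% of trials.
- 20% (upper bound, all losses before week 4): it switches in about 100%, with power 4–5 points below a fixed t test.

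Across the two settings the power loss is 1–5 points. The exact rates move with the assumed means and correlation, but the direction does not.

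**The case against.** The strongest reply is that nobody chooses the favourable test. The rule is written in advance and applied by a statistician blind to allocation, type I error stays near 5%, and with complete data the switch is rare and hardly ever alters the conclusion. All of that stands. A reader might infer from a switching rule that the primary estimand is picked after seeing results, or that the error rate is compromised. The documents do not support either reading.

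Two further inferences also fail. One is that a bounded scale will almost always fail a normality test. That may be true of the week-8 score, but the Sample size calculation section makes the primary variable the change, for which rejection with complete data is near the false-positive rate. The other is that the switch is what prevents adjustment for baseline or centre. The t test on the other branch is equally unadjusted.

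It is also fair to say that the normality criterion and the name of the rank test may sit in a fuller document, so their absence is not the point here. Nor is the power loss general: in the skewed case of step 3 the rank test gained power. A rank analysis can carry a location-shift estimate with an interval, and the article does not rule one out. The summary it does specify on that branch, however, is medians with ranges.

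The reply does not remove two things. The article itself ties the primary summary to the observed distribution while sizing the trial on a mean difference. And the reassurance about rarity assumes complete data, whereas the plan's own imputation rule can make the rank branch the usual route.

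**Conclusion.** The point holds as a matter of interpretation and consistency with the sample size. As written, the primary result may be summarised by medians with ranges when the trial was sized on a 10-point mean difference. The size depends on early dropout: about 9–12% of trials would switch with complete data, about 80–95% if 10% of patients have baseline carried forward, and about 100% at the 20% upper bound. In those carried-forward settings the power cost is 1–5 points against a fixed t test. Type I error is not materially inflated.

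These rates rest on an assumed Shapiro-Wilk rule by arm, an assumed 0–100 scale, and assumed means, baseline SD and correlations, none of which the article states. The mismatch between the two sections needs none of these assumptions. The point should be corrected, but it does not threaten the trial's validity.

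**What to change.** Delete the distribution-based switch for the primary outcome. State that MBI at 8 weeks is compared as a difference in means with 95% confidence interval, adjusted for baseline MBI by ANCOVA, whatever the observed distribution. With baseline as a covariate, the treatment estimate is the same whether the outcome is the 8-week score or the change, so the primary variable is preserved. Keep a named rank-based test as a sensitivity analysis only. Robust or bootstrap standard errors are optional.

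The cost is about two sentences in the Statistical analysis section. No new data are needed, and the calculation of about 150 per group stands because it is already on the mean-difference scale.
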